### 3.1.1. Stage 1 – Preliminary safety and feasibility study

In Stage 1, the feasibility, safety and tolerability of point-of-care G6PD testing and PQ7 in G6PD normal (>70%) patients will be determined in 4 selected health facilities with staff undertaking clinical review on day 3 and also day 7 to ensure patient safety. Stage 2 will only proceed after review of the Stage 1 data by SRT and SMC.

After 3 months, the revised case management will be rolled out at 4 selected sites (2 in Indonesia and 2 in PNG), initiating Stage 1. The remaining sites will continue the Pre-Implementation Stage. Stage 1 is anticipated to last 6 months, during which a total of 800 patients with *P. vivax* malaria (~500 from Indonesia and ~300 from PNG) will be treated (Figure 1).

All patients that are eligible for and consent to participate in the study, will be tested by quantitative G6PD activity assessment using the G6PD STANDARD (SD biosensor, ROK). Patients with G6PD activity >70% ( $\geq 6.1$  U/gHb) will be prescribed primaquine at a total dose of 7 mg/kg over 7 days (PQ7) and those with 30-70% activity (4.1-6.0 U/gHb) will be prescribed the same total dose of primaquine over 14 days (PQ14). Patients with G6PD activity <30% ( $\leq 4.0$  U/gHb) will be prescribed primaquine at a dose of 0.75 mg/kg/week for 8 weeks (PQ8w).

The safety review team (SRT) will review all AESI (adverse event of special interest) and SAE (severe adverse event) data after every 100 patients treated with primaquine and may request to review additional data if there are safety concerns. A formal interim analysis is planned after enrolment of 400 patients (~150 patients from PNG, ~250 patient from Indonesia). The SRT will review the interim analysis outputs and share with the Safety Monitoring Committee (SMC) who will conduct an interim review and issue a recommendation regarding continuation of Stage 1.

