### 9.1. Stage 1 – Preliminary safety and feasibility study

For Stage 1, the number and proportion of patients experiencing at least one SAE (S1.PE1) or at least one AESI (S1.PE2) will be computed by treatment arm (PQ7, PQ14, PQ8w), and described in summary tables which will include breakdown by type of event, severity, relatedness to treatment, and timing of occurrence (see Appendix 4 for example Tables 1-4). The number and proportion of patients permanently discontinuing treatment (S1.SE4) will be computed by treatment arm and presented in a summary table, with breakdown of reason for discontinuation. Absolute numbers of AESIs with denominators (S1.PE1-3) and proportions with 95% confidence intervals (calculated using a binomial distribution) will be presented in tabular and graphical format. A full tabulation of all SAEs will also be presented.

For S1.EE3, the number and proportion (and 95% Confidence Interval) of patients observed to have a >25% reduction in haemoglobin to a concentration below 7 g/dl will be computed by treatment arm (PQ7, PQ14, PQ8w), and described in summary tables.

For S1.EE1 and S1.EE2, the unadjusted and adjusted mean absolute and proportional maximum change in haemoglobin within 7 days (95% CI) respectively will be presented by treatment arm (PQ7, PQ14, PQ8w). The adjusted means will be estimated from a linear regression model that adjusts for baseline haemoglobin level and G6PD enzyme activity level. The association between change in haemoglobin from baseline to day 2 and G6PD enzyme activity level will be estimated from a linear regression model that allows for a nonlinear association using fractional polynomials and adjusts for baseline haemoglobin level, age, sex and baseline parasitaemia. A scatterplot of the data will be presented with observations labelled by treatment arm (PQ7, PQ14, PQ8w).

For S1.EE4, the mean difference, standard deviation of the difference and 95% limits of agreement between Biosensor and HemoCue haemoglobin measurements will be computed using Bland-Altman plots (Bland JM & Altman DG 1995), stratified by day of measurement (day 0, 3, 7) and country. The data will be presented in tabular and graphical formats.

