For S1.EE5, the distribution of methaemoglobin at baseline, day 3 and day 7 will be presented by treatment arm (PQ7, PQ14, PQ8w) using box and whisker plots. The distribution of methaemoglobin levels at day 7 will be compared between the PQ7 (daily PQ dose of 1mg/kg) and PQ14 (daily PQ dose of 0.5 mg/kg) treatment arms using linear regression after adjusting for baseline haemoglobin concentration, parasitaemia, age, sex, and G6PD enzyme activity level.

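### Stage 1 haemoglobin arm means and the PQ7–PQ14 methaemoglobin contrast are adjusted for G6PD activity, the variable that assigns the arm, so the adjusted PQ14 and PQ8W means and all arm contrasts depend on an assumed G6PD curve

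*SAP*

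**What the plan says.** **Assignment (SAP Section 3.1.1).** Among enrolled patients the regimen follows the G6PD result. The highest band, from 6.1 U/gHb upward, is given PQ7. In the middle band (4.1–6.0 U/gHb) each patient "will be prescribed the same total dose of primaquine over 14 days (PQ14". In the lowest band (at most 4.0 U/gHb) each patient "will be prescribed primaquine at a dose of 0.75 mg/kg/week for 8 weeks (PQ8w".

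**Haemoglobin, S1.EE1 and S1.EE2 (Section 9.1).** "the unadjusted and adjusted mean absolute and proportional maximum change in haemoglobin within 7 days (95% CI) respectively will be presented by treatment arm". The next sentence gives the model: "The adjusted means will be estimated from a linear regression model that adjusts for baseline haemoglobin level and G6PD enzyme activity level". Section 9.3 repeats this and treats G6PD activity as a potential confounder. Section 7 lists G6PD activity among the covariates for safety and exploratory outcomes.

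**Methaemoglobin, S1.EE5 (Section 9.1).** Day 7 levels are compared between PQ7 and PQ14, which the SAP labels by daily dose (1 and 0.5 mg/kg), "using linear regression after adjusting for baseline haemoglobin concentration, parasitaemia, age, sex, and G6PD enzyme activity level".

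**What is not stated.** For these models the SAP gives no G6PD value at which the adjusted means are evaluated, no functional form for the G6PD term, and no warning that the contrasts depend on the model. A non-linear G6PD term (fractional polynomials) is specified only for the separate analysis of haemoglobin change against G6PD.

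**The concern.** A confounder can be adjusted for when the groups share some of its range. Here G6PD activity is the assignment rule, and the planned ranges do not meet. To give a PQ14 or PQ8W mean at a G6PD value typical of the cohort, the model must extend a fitted line or curve into a region where those arms have no planned patients. The arm contrast is then whatever remains after that extension, and the data can hardly test whether the curve is right.

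Two interpretations are at stake. For S1.EE1 and S1.EE2, an adjusted mean printed beside an unadjusted one is usually read as the better estimate of haemoglobin fall in that arm, which here it is not. For S1.EE5, the PQ7–PQ14 contrast invites reading as a dose effect, and curvature in the G6PD relation can produce such a contrast when no dose effect exists.

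**Working it through.** The SAP gives no figure for this point, so there is none to reproduce. The check has a structural part and an illustrative part.

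**1. Overlap by design (Section 3.1.1).** The highest PQ14 value is 6.0 and the lowest PQ7 value 6.1 U/gHb. The highest PQ8W value is 4.0 and the lowest PQ14 value 4.1. Planned overlap is zero. Overlap can come only from off-algorithm prescribing, which Table S1 counts as protocol deviations.

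**2. Distance of extrapolation.** Arm sizes: Section 3.1.1 expects 700 PQ7 and 100 PQ14; Section 4.1 assumes 764 of 800 eligible for PQ7. The SAP gives no G6PD distribution, so I assume PQ7 truncated normal from 6.1 U/gHb (mean/SD parameters 7.5/1.5 to 9.5/2.5) and PQ14 uniform on 4.1–6.0. With 700/100 the overall mean G6PD is about 7.6 to 9.3. An adjusted PQ14 mean at that point lies 7.6 − 6.0 = 1.6 to 9.3 − 6.0 = 3.3 U/gHb above any value in the PQ14 band. PQ8W lies further off. The PQ7 mean is inside its own range.

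**3. What the adjusted means do.** Assumed: 764/24/12 patients, PQ7 truncated normal (8, SD 1.8), PQ14 uniform 4.1–6.0, PQ8W uniform 1–4, residual SD 1, fall dependent on G6PD only. At equal G6PD the true arm difference is therefore zero in every row. Values are fall in g/dL for PQ7 / PQ14 / PQ8W.

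| G6PD relation | True arm means | G6PD-adjusted means | PQ8W minus PQ7, true → adjusted |
|---|---|---|---|
| Linear, 0.15 per U | 0.68 / 1.19 / 1.58 | 0.71 / 0.72 / 0.72 | 0.90 → 0.01 |
| Exponential | 0.72 / 1.01 / 1.77 | 0.72 / 0.89 / 1.53 | 1.05 → 0.81 |
| Effect only below 6.1 | 0.75 / 1.17 / 2.20 | 0.75 / 1.16 / 2.16 | 1.45 → 1.41 |

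The same model removes all, some or almost none of the arm difference, according to a shape that cannot be separated from arm.

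**4. False PQ7–PQ14 differences.** Model: outcome = intercept + arm + linear G6PD, no true arm effect, 700/100, PQ7 parameters 8.5/2.0, residual SD 1, 2,000 runs.

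| G6PD relation (g in U/gHb) | Mean arm estimate | SE | Runs with p < 0.05 |
|---|---|---|---|
| −0.15g | 0.00 | 0.138 | 4.4% |
| 3·exp(−g/3) | −0.19 | 0.139 | 26% |
| −0.4·min(g, 7) | −0.66 | 0.139 | 99.7% |

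Hand check: 0.187/0.139 = 1.35, and Φ(1.35 − 1.96) ≈ 0.27. For the plateau, 0.663/0.139 = 4.77, and Φ(4.77 − 1.96) ≈ 0.998. A separate simulation gave 5% (linear), about 11–21% (exponential) and 79–99% (plateau). Together these give the 11–26% and 79–99.7% used here. They illustrate the problem and are not limits.

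**5. Cost in precision.** The unadjusted SE is √(1/700 + 1/100) = 0.107, against 0.138 adjusted, a ratio of 1.29. The variance inflation is 1.65–1.76 with 700/100 and 1.23–1.28 with 764/36. The model can be fitted; collinearity is not the main fault.

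**6. Off-algorithm patients.** If 2–5% of patients are prescribed off the algorithm, about 2–5 patients in the PQ14 band receive PQ7 with 700/100, and about 1–2 with 764/36. The plateau bias shrinks but stays: −0.33 to −0.55 and −0.24 to −0.47 respectively.

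**The case against.** Several points on the other side stand.

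- **Planned safeguards.** A reader might infer that the adjusted means will conceal a larger haemoglobin fall in low-G6PD patients. The SAP does not support that. Section 9.1 also plans unadjusted arm means, a scatterplot labelled by arm, a fractional-polynomial G6PD analysis, the S1.EE3 proportions by arm, and SAE and AESI proportions by arm. Section 6.1 adds analyses by G6PD band.
- **Linear case.** A reader might take the vanishing gradient in the first row of step 3 as bias. If the relation is exactly linear with a common slope, the arm term is unbiased. It answers how the regimens compare at equal G6PD, which is a different question from how far haemoglobin fell in each arm.
- **Not every value is an extrapolation.** At the cohort mean G6PD, the PQ7 mean is supported by its own data.
- **Functional form.** The SAP does not say that G6PD enters as a straight line, and in the next sentence it uses the term linear regression for a fractional-polynomial model. Flexible terms might reduce misfit near the cut-off, but they cannot create overlap. If G6PD were entered as a category, it would coincide with arm among correctly treated patients.
- **S1.EE5 without G6PD.** Dropping G6PD leaves dose fully mixed with G6PD status, so neither version is a clean dose comparison.
- **Status and size.** All three endpoints are exploratory and S1.EE5 is post hoc. Section 5.1 says methaemoglobin was measured routinely only in Papua, from midway through Stage 1. The S1.EE5 sample will thus be smaller than I simulated: rejection rates would be lower, but the bias would not shrink for that reason.

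None of these supplies common support between arms, so the core of the point stays.

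**Conclusion.** The plan is wrong as written on this point, with limited consequences. The bands in Section 3.1.1 and the adjustment sets in Sections 9.1 and 9.3 together make the adjusted PQ14 and PQ8W means, and all G6PD-adjusted arm contrasts, dependent on a G6PD shape that the data cannot check across arms. That conclusion follows from the SAP alone.

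The size rests on assumed G6PD distributions, residual SD and curves. With no true arm effect, a false PQ7–PQ14 difference appeared in about 5% of runs (linear), 11–26% (exponential) and 79–99.7% (plateau at 7 U/gHb). The documents do not say which shape holds. The primary Stage 1 safety proportions are unaffected.

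**What to change.** **S1.EE1 and S1.EE2 (Sections 9.1 and 9.3, and Section 7 for these models).** Adjust the arm means for baseline haemoglobin, with age, sex and parasitaemia if wished, but not for G6PD activity. Describe arm differences as the combined effect of regimen and G6PD stratum. Leave the G6PD relation to the fractional-polynomial analysis and scatterplot already planned.

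**S1.EE5 (Section 9.1).** Report the PQ7–PQ14 difference twice: without G6PD, labelled as mixed with G6PD status; and with G6PD, labelled as a model-dependent contrast at the 70% cut-off. State the G6PD term used in the second version.

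**Cost.** Wording in three sections, one covariate fewer in two models, and one extra estimate for S1.EE5. No data collection, regimen or primary analysis changes. The price is that arm differences cannot be read as pure dose effects, but the assignment rule already prevents that reading.

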## 7 Outcomes and Covariates

The primary, secondary and exploratory outcomes for Stage 1 and Stage 2 are defined in Section 2.2 (Endpoints).

Intervention and covariate variables for analyses of the impact of the implementation package on incidence of symptomatic *P. vivax* malaria (effectiveness outcome S2.SE15) will be defined as follows:

- a) **Level change** intervention effect (i.e. change in mean monthly incidence) 6 months after the start of stage 2; Figure 2, Section 9.
- b) **Slope change** intervention effect (i.e. change in the rate of change of monthly incidence) immediately after the start of stage 2; Figure 2, Section 9.

Intervention will take the value of 1 for all time points following the start of stage 2 implementation at each health facility site, and a value of 0 for all other timepoints for both the level and slope changes.

The time month covariate will be defined as the number of months after the start of stage 2 implementation (Appendix 4: Figure 1), i.e. negative values for pre-implementation and positive values for post-implementation.

Seasonality will be captured using spline terms for the Indonesian health facility sites and the PNG health facility sites.

Any unexpected stock outages or major, discrete malaria control interventions external to the SCOPE project will also be captured and reported by health facility site and calendar time month.

The key covariates that will be included in the analyses of the safety and exploratory outcomes will be the haemoglobin concentration at enrolment, the mg/kg dose of primaquine and the G6PD enzyme activity. Key covariates to be adjusted for in the analysis of patient-level effectiveness outcomes will be baseline age, weight and sex, except in the case that these variables have already been considered in a propensity score matching process.

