## 9.3 Measures to Adjust for Confounders, Heterogeneity and Autocorrelation

### Confounders

Both pre- and post-implementation surveillance periods will be of sufficient duration to minimise the risk of outlier seasonal and social events on the incidence of vivax malaria. Multivariable models, controlling for known potential confounders such as sex, age, weight, calendar month and seasonality will be used for comparisons of malaria incidence, slide positivity and other indices. For the exploratory outcomes, S1.EE1 and S1.EE2 multivariable linear regression models will be adjusted for known potential confounders, baseline haemoglobin levels and G6PD enzyme activity level.

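### The Stage 1 curve of day-2 haemoglobin change on G6PD activity pools three regimens with no dose term, so it mixes G6PD activity with dose

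*SAP*

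**What the plan says.** The model is in SAP Section 9.1, in the paragraph on S1.EE1 and S1.EE2: "The association between change in haemoglobin from baseline to day 2 and G6PD enzyme activity level will be estimated from a linear regression model". The same sentence says that the model "allows for a nonlinear association using fractional polynomials and adjusts for baseline haemoglobin level, age, sex and baseline parasitaemia". Treatment arm enters only as a label on the accompanying scatterplot. No restriction or stratification by arm is stated for the fit.

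Two other sections bear on the covariates, and they differ:

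- Section 7 gives the key covariates for the safety and exploratory outcomes as "the haemoglobin concentration at enrolment, the mg/kg dose of primaquine and the G6PD enzyme activity".
- Section 9.3, under Confounders, says "S1.EE1 and S1.EE2 multivariable linear regression models will be adjusted for known potential confounders, baseline haemoglobin levels and G6PD enzyme activity level". Dose is not named.

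Section 3.1.1 sets the regimen from the G6PD result: PQ7 at 6.1 U/gHb or more, PQ14 at 4.1 to 6.0, and PQ8W at 4.0 or less. Section 1.1 states that the higher daily dose of the 7-day regimen carries more haemolysis.

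**The concern.** The exposure on the horizontal axis decides the dose. Patients with low activity get less primaquine in the first days, so part of any smaller haemoglobin fall among them reflects the smaller dose. A model without dose assigns that part to G6PD activity. Dose also changes in steps at the band limits, which one smooth curve cannot follow.

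What is at stake is the reading of one exploratory curve. A reader who takes it as the effect of G6PD activity on haemoglobin loss could see a weak or flat relation at low activity when, at a fixed dose, the fall there is larger. The SAP also leaves the analyst with two conflicting instructions on whether dose belongs in the model.

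**Working it through.** The SAP gives no figure for this model, so there is none to reproduce. The check is a comparison of the covariate lists (above), a dose calculation, and an illustration of size.

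**Scheduled dose by day 2.** The regimens are 1.0 mg/kg/day (PQ7), 0.5 mg/kg/day (PQ14) and 0.75 mg/kg once a week (PQ8W). With two or three daily doses taken:

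- PQ7: 2 × 1.0 to 3 × 1.0 = 2.0 to 3.0 mg/kg
- PQ14: 2 × 0.5 to 3 × 0.5 = 1.0 to 1.5 mg/kg
- PQ8W: 0.75 mg/kg

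Highest to lowest band: 2.0/0.75 = 2.7 to 3.0/0.75 = 4.

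**Illustration of size.** None of the following assumptions is in the SAP. Let the fall in g/dl at activity g be

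fall = 0.9q + f × [0.9(1 − q) + 0.10 × (7 − g)],

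where q is the share of the fall at 7 U/gHb that does not depend on dose, and f is the dose relative to PQ7 after three daily doses (1, 0.5 and 0.25). At PQ7 dose (f = 1) the true fall is 0.9 + 0.10 × 4.5 = 1.35 at 2.5 U/gHb, 1.10 at 5 and 0.90 at 7, whatever q is.

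The as-treated column is arithmetic. For example, at 2.5 U/gHb with q = 0.5: 0.45 + 0.25 × (0.45 + 0.45) = 0.68. The last column is the mean of the best second-degree fractional polynomial over simulated datasets of 700/85/15 patients on PQ7/PQ14/PQ8W, with residual SD 1 g/dl and no dose term.

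| q | True fall at PQ7 dose (2.5, 5, 7 U/gHb) | As-treated fall | Pooled curve |
|---|---|---|---|
| 0 | 1.35, 1.10, 0.90 | 0.34, 0.55, 0.90 | 0.26, 0.71, 0.81 |
| 0.5 | 1.35, 1.10, 0.90 | 0.68, 0.78, 0.90 | 0.74, 0.88, 0.85 |
| 0.75 | 1.35, 1.10, 0.90 | 0.84, 0.89, 0.90 | 0.92, 0.95, 0.86 |

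So 1.35 is fitted as about 0.3 to 0.9. Changing the assumed G6PD distribution moved the value at 2.5 U/gHb by up to about 0.1. The curve turns over clearly at q = 0, mildly at q = 0.5, and is nearly flat at q = 0.75.

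With no G6PD effect and q = 0, the true fall at PQ7 dose is 0.90 everywhere, but the as-treated fall at 2.5 U/gHb is 0.25 × 0.90 = 0.23, so low activity looks protective.

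A straight line over all arms (q = 0) has slope about −0.03 g/dl per U/gHb against a true −0.10. A line in PQ7 patients alone gives −0.10.

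**Would adding dose to the pooled model be enough?** Only in part. In a separate simulation, with a true change of −1.65 g/dl at 2 U/gHb and 3 mg/kg, the pooled curve without dose gave −0.35. With a mg/kg term it gave −1.26, with an SD of about 0.3. Regimen is nearly a function of G6PD, so the two separate only through variation within bands and the form of the model.

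**The case against.** Five points can be made on the other side.

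- **Section 7 already names dose.** This stands. A reader might infer that the SAP has decided to leave dose out. The documents support only an inconsistency between Section 7 and Sections 9.1 and 9.3. The one model written out for this association still omits dose.
- **Section 6.1 plans regimen subgroups.** Regimen and G6PD band are prespecified subgroups for secondary analyses of patient-related outcomes, so a PQ7-only fit could be read into the plan. It would be secondary, and the pooled curve would remain the stated estimate.
- **Section 9.1 promises only an association.** Haemoglobin change under G6PD-guided treatment is a legitimate descriptive target, and the pooled curve tracks the as-treated values to within about 0.16 g/dl in the table. This stands, but the SAP does not say that this is the target.
- **The size rests on assumptions.** This stands. The SAP expects 700 PQ7 and 100 PQ14 patients in Section 3.1.1, assumes 764 eligible for PQ7 in Section 4.1, and gives no PQ8W number. The fit at 2.5 U/gHb rests on few patients in any split.
- **Readers will see the arms.** Section 9.1 also gives adjusted means by arm and a scatterplot labelled by arm, which limits the harm. Neither changes the fitted curve.

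**Conclusion.** The point holds as a minor correction to an exploratory analysis. As written in Section 9.1, the curve mixes G6PD activity with dose. It is attenuated at low activity relative to a fixed dose and can flatten or turn over. The direction of this bias follows from the dosing rule in Section 3.1.1 and the dose-haemolysis statement in Section 1.1. The figure of about 0.3 to 0.9 g/dl fitted for a true 1.35 is illustrative and rests on the assumed arm sizes, G6PD distribution, effect of G6PD and dose-independent share.

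Two stronger readings are not supported:

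- A reader might infer that the curve will always reverse. Reversal needs much of the early fall to be dose-driven. With a steeper slope of 0.20 per U/gHb and three-quarters of the fall at 7 U/gHb independent of dose, the as-treated falls at 2.5, 5 and 7 U/gHb are 0.96, 0.99 and 0.90, which is attenuated but not reversed overall.
- A reader might infer that the curve bears on the choice of G6PD thresholds. No section says so. The thresholds are fixed in Section 3.1.1, where progression rests on committee review against criteria set in advance.

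**What to change.** - Reconcile Sections 7, 9.1 and 9.3 so that one covariate list applies to this model.
- In Section 9.1, fit the fractional-polynomial curve in PQ7 patients, with mg/kg dose as a covariate beside those already listed.
- Show PQ14 and PQ8W separately, with their own fits or descriptively, and with their intervals.
- If a pooled curve is kept, label it as haemoglobin change under G6PD-guided treatment as given, and state that it does not estimate the effect of G6PD activity.

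The cost is SAP wording and a little more analysis of data already collected. The downside is that the modelled curve covers only 6.1 U/gHb and above. The lower range, about 100 patients on the Section 3.1.1 expectation, will be imprecise.
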